# Internet-Delivered Cognitive Behavioral Treatment for Chronic Pain in Adolescent Survivors of Childhood Cancer: Protocol for a Single-Group Feasibility Trial

**DOI:** 10.2196/45804

**Published:** 2023-08-01

**Keywords:** pediatric oncology, chronic pain, cognitive behavioral therapy, eHealth, intervention, late effects, cancer survivorship, pediatric cancer, youth, mental health, psychological difficulties, chronic health conditions, pain management, intervention, cancer survivor

## Abstract

**Background:**

There are over 500,000 survivors of childhood cancer in North America alone. One in 4 survivors experiences chronic pain after treatment has been completed. Youths with chronic pain report increased anxiety, depression, activity limitations, and sleep disturbances. An 8-week web-based cognitive behavioral treatment for chronic pain (Web-Based Management of Adolescent Pain [WebMAP]) has demonstrated a reduction in pain in youths but has not yet been explored in survivors.

**Objective:**

The objectives of this study are to (1) test the feasibility and acceptability of WebMAP for a sample of survivors with chronic pain and their parents; (2) assess the acceptability of WebMAP using qualitative interviews; (3) assess WebMAP’s effect on activity limitations, pain intensity, depression and anxiety symptoms, and sleep disturbances; and (4) assess WebMAP’s effect on parent pain catastrophizing and parental response to their child’s pain.

**Methods:**

A single-arm mixed methods pre-post intervention study design will be used. Participants will be 34 survivors and at least one of their parents or caregivers. Inclusion criteria are (1) a cancer history, (2) current age of 10-17 years, (3) >2 years post treatment or >5 years post diagnosis, (4) pain present over prior 3 months impairing >1 area of daily life and occurring >1 time per month, and (5) computer access with broadband internet. Survivors will complete a pretreatment questionnaire, which will include the following: the Child Activity Limitations Interview, the pain intensity Numerical Rating Scale, Patient-Reported Outcomes Measurement Information System (PROMIS)–Pain Interference, Anxiety, Depression, Insomnia Severity Index, and Adolescent Sleep Wake Scale. Parents will complete the Pain Catastrophizing Scale–Parent Version and the Adult Responses to Child Symptoms. Upon completion of pretreatment questionnaires (T0), survivors will begin WebMAP. After the 8-week intervention, survivors will complete the same measures (T1), and at 3-month follow-up (T2). Posttreatment interviews will be conducted to determine acceptability. Feasibility will be assessed via recruitment and retention rates. Treatment engagement will be measured by number of modules completed. Pre-post outcome data will be assessed using linear mixed models. Qualitative data will be analyzed using thematic analysis. Patient partners will be involved in study design, recruitment, interpretation of results, and knowledge translation.

**Results:**

This study has been funded in January 2022. Data collection started in May 2022 and is projected to end in August 2023. We have enrolled 10 participants as of December 2022.

**Conclusions:**

Investigating whether WebMAP is useful to survivors will be an important step in improving pain management in this population.

**Trial Registration:**

ClinicalTrials.gov NCT05241717; https://clinicaltrials.gov/ct2/show/NCT05241717

**International Registered Report Identifier (IRRID):**

DERR1-10.2196/45804

## Introduction

Currently, there are over 500,000 survivors of pediatric cancer in North America alone [1]. Unfortunately, two-thirds of survivors of childhood cancer will experience late- and long-term effects from their cancer and its treatments, such as subsequent chronic health conditions and psychological difficulties [2]. Our previous work demonstrated that approximately 1 in 4 survivors of childhood cancer experiences chronic pain after treatment completion and 1 in 5 experiences moderate to severe chronic pain problems, reporting high pain intensity and interference in activities [3]. We also found survivors living with chronic pain reported significantly worse depressive and anxiety symptoms and poorer quality of life than survivors without chronic pain [3,4].

Survivors of childhood cancer are already at risk for worse mental health than their healthy peers as a result of cancer and its often toxic treatments [2], and pain could exacerbate these outcomes. Importantly, pain among survivors of childhood cancer has been shown to persist into adulthood, which among noncancer adolescents has been linked to lower educational and social attainment and poor vocational functioning in young adulthood [5]. With the growing number of survivors of childhood cancer, improving long-term follow-up care will help improve health care for these vulnerable youths by reducing their risk of continued pain and poor health into adulthood.

Chronic noncancer pain in childhood is associated with negative developmental outcomes in young adulthood including a higher likelihood of dropping out of high school, a lower likelihood of graduating from university, poor vocational functioning, and social impairments [6]. A large, longitudinal study demonstrated that chronic pain in adolescence conferred risk for lifetime anxiety and depressive disorders [6].

According to the United Nations Office on Drugs and Crime’s most recent World Drug Report, approximately 585,000 people experienced drug-related deaths and the majority of these deaths could be attributed to opioids [7]. Importantly, there is little evidence for the efficacy of prescription opioids for the treatment of chronic pain, and long-term opioid use for the treatment of chronic pain can cause adverse effects such as overdose, cardiovascular events, and motor vehicle accidents [8,9]. Chronic pain is also a significant financial burden on families, society, and the health care system, costing up to CAD $60 billion (US $46.99 billion) per year in Canada [10], and is one of the most common reasons for seeking health care [11,12]. According to a recently proposed developmental model of chronic pain, strategies for pain prevention and management should begin in childhood and should leverage psychological interventions in order to prevent pain-related morbidities and promote better overall well-being in adulthood [13]. Thus, research on nonpharmacological pain management strategies is needed in general, particularly in this underserved population.

While the prevalence of pain is high in survivors of childhood cancer, no evidence-based interventions for pain are available for youth survivors of childhood cancer [14]. Most promising for this population may be cognitive behavioral therapies, as they can effectively target activity limitations, depression and anxiety symptoms, and sleep disturbances related to pain. Cognitive behavioral therapies are effective in reducing the burden of pain in youths with chronic noncancer pain conditions [15]; however, there are also significant barriers to participation in clinic-based cognitive behavioral therapy programs. For example, parents may have to take time off work and take their children out of school to visit a psychologist (the professionals most often trained and competent to deliver cognitive behavioral therapy), a psychologist may not be affordable, or there may not be a psychologist available in some areas.

In response to these limitations and barriers, internet-delivered cognitive behavioral therapy (CBT) can address these significant barriers and has demonstrated feasibility and efficacy in youths with chronic pain [16]. An 8-week web-based cognitive behavioral therapy program called web-based management of adolescent pain (WebMAP) has been rigorously developed and tested in children and adolescents with various chronic pain conditions, and is feasible and acceptable for this group, demonstrating clinically significant reductions on primary targets including activity limitations and pain intensity [17,18]. In addition, previous trials with WebMAP have shown economic benefits for both intervention and education groups, demonstrating a significant decrease in health care–related expenditures from the year before participating in the trial to the year after [19]. In other populations, WebMAP has demonstrated feasibility and acceptability in adolescents with sickle cell disease and their parents, with no indication that the program needed to be significantly tailored for those with sickle cell disease [20].

Treatment for chronic pain in youths is enhanced by the inclusion of parents, given the developmentally important role they play in their child’s life. For example, unique social factors exist related to parent and family influences on pediatric chronic pain and disability such as parental responses to child pain behavior, parenting style, family environment, and overall family communication and functioning [21]. Parent pain catastrophizing has also been shown to play an important role in their child’s pain interference [22,23]. Parent protectiveness is also related to important child-level outcomes (eg, child functional disability) in trials assessing family cognitive behavioral therapy for adolescents with chronic pain [24]. WebMAP includes a parent component in which parents complete modules in parallel with their child in order to target these factors. In WebMAP, parents are taught various operant strategies to respond to their child’s pain behaviors. In previous trials with WebMAP, parent distress, and parent protective behaviors predict child functional disability trajectories 6- and 12-months post treatment [25], and parent engagement in the program may also be predictive of treatment outcomes [26]. Thus, the inclusion of parents in psychological intervention trials for youths with chronic pain is recommended.

WebMAP has never been tested on a sample solely comprised of youths with a history of cancer. Thus, the primary objective of this study is to test the acceptability and feasibility of WebMAP for survivors of childhood cancer living with chronic pain and their parents, using a single-arm, pretest-posttest mixed methods design with semistructured interviews. Objective 1 will test the feasibility and acceptability of WebMAP for a sample of survivors with chronic pain and their parents. We hypothesize that the intervention will be feasible, that families will be engaged in the treatment and it will be safe. Objective 2 will assess the acceptability of WebMAP using qualitative interviews. Objective 3 will assess WebMAP’s effect on activity limitations, pain intensity, depression and anxiety symptoms, and sleep disturbances. We hypothesize that survivors of childhood cancer participating in WebMAP will report significantly reduced activity limitations, pain, anxiety and depressive symptoms, and sleep disturbances from before to after the intervention. Finally, objective 4 will assess WebMAP’s effect on parent pain catastrophizing and parental response to their child’s pain. We hypothesize that parents participating in WebMAP will report significantly reduced catastrophizing about their child’s pain, distress, and reduced protective parental responses to their child’s pain. This study protocol follows the Standard Protocol Items: Recommendations for Interventional Trials Checklist for recommended items to address in a clinical trial protocol [27].

## Methods

### Study Design

This study will use a single-arm, mixed methods, pre-post design. Survivors of childhood cancer with chronic pain will participate in an 8-week internet-delivered cognitive behavioral therapy intervention (WebMAP). Assessment questionnaires will be collected before the intervention (T0), immediately following the intervention (T1), and 3-months after intervention completion (T2). Individual interviews will also be conducted upon completion of the intervention.

### Participants

#### Sample Size

Based on an audit of sample sizes of combined feasibility and pilot trials in similar populations, median sample sizes ranged from 30 to 36 [28]. A sample of 34 will be sufficient to detect an effect size (Cohen *d*) of 0.4 with our preliminary outcomes with 80% power and α at .05. Therefore, we will aim to recruit a total sample of 38 to conservatively account for 10% attrition over the study duration.

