### Data Analysis

#### Quantitative Data Analysis

To address objective 1, we will use frequencies and descriptive statistics to describe recruitment and retention rates, treatment adherence, and acceptability. To address objectives 2 and 3, primary efficacy end points of the study will be calculated as within-person changes in outcome measures using Cohen *d* effect sizes from T0 to T1 and T2. Outcome data will be analyzed using paired samples *t* tests in order to assess changes in outcome variables over time. Treatment effect sizes (Cohen *d*) will be calculated for changes in means, standardized by the pooled SD. All quantitative analyses will be conducted using SPSS (version 27; IBM Corp).

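### The 80% power claimed for 34 participants cannot be reproduced for the planned paired t test unless an unstated, favourable pre-post correlation is assumed

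*Protocol article*

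**What the plan says.** The Sample Size section gives two grounds for the number. The first is an audit of comparable feasibility and pilot trials, with median sizes of 30 to 36. The second is a power statement, which opens "A sample of 34 will be sufficient to detect an effect size" and puts that effect, as Cohen d, at 0.4 for the preliminary outcomes, with power of 80% and alpha of .05. The target is then raised to 38 for 10% attrition.

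The power statement does not say which test it is for, whether alpha is one- or two-sided, which SD scales d, or what pre-post correlation was assumed. Other sections supply part of this:

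- Study Design: "This study will use a single-arm, mixed methods, pre-post design", with assessments at T0, T1 and T2.
- Quantitative Data Analysis: "Outcome data will be analyzed using paired samples" t tests, and effect sizes "will be calculated for changes in means, standardized by the pooled SD".
- Abstract, Methods: "Pre-post outcome data will be assessed using linear mixed models", which is a different analysis from the one in the body.

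**The concern.** A paired t test draws its power from the mean change divided by the SD of the within-person differences. The article defines d by the pooled SD of the scores. The two scales agree only when the pre-post correlation is 0.5, and at that value 34 pairs fall well short of 80% for d = 0.4. The sentence nevertheless gives 80% without any condition.

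What is at stake is how the efficacy results are read. The article hypothesises significant reductions in the survivor and parent outcomes, and it makes encouraging early efficacy part of the case for a later efficacy trial. A reader told that power is 80% expects a true effect of 0.4 to be missed 20% of the time. At 62% power it is missed about 38% of the time (100 − 62).

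**Working it through.** **Inputs.** n = 34, d = 0.4, alpha = .05 and a target of 80% (Sample Size); paired t test and pooled-SD scaling (Quantitative Data Analysis); one group (Study Design). Sidedness and the pre-post correlation r are not given, so both are varied here as assumptions.

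**Step 1: the attrition step reproduces.** 34 / (1 − 0.10) = 37.8, rounded up to 38.

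**Step 2: try to reproduce 80%, taking 0.4 as the change in units of the SD of the differences (dz).** Power comes from the noncentral t distribution with df = n − 1 = 33 and noncentrality dz × √n = 0.4 × √34 = 2.33.

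| Complete pairs | Two-sided | One-sided |
|---|---|---|
| 34 | 62.0% | 73.9% |
| 38 (no attrition) | 67.1% | 78.1% |

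As a check, the normal approximation for 34 pairs, two-sided, is Φ(2.33 − 1.96) = 64.5%. Reaching 80% needs 52 pairs two-sided or 41 one-sided. On this reading neither sidedness reaches 80%, even with all 38 recruits retained.

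**Step 3: take 0.4 on the pooled SD, as the analysis section defines it.** With equal SDs before and after, the SD of the differences is SD × √(2(1 − r)), so dz = d / √(2(1 − r)). For r = 0.6, dz = 0.4 / √0.8 = 0.447.

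| Assumed r | dz | Two-sided power, n = 34 | One-sided power, n = 34 | Pairs for 80%, two-sided |
|---|---|---|---|---|
| 0.3 | 0.338 | 48.2% | 61.2% | 71 |
| 0.4 | 0.365 | 54.3% | 67.0% | 61 |
| 0.5 | 0.400 | 62.0% | 73.9% | 52 |
| 0.6 | 0.447 | 71.6% | 81.8% | 42 |
| 0.67 | 0.492 | 79.6% | 87.8% | 35 |
| 0.7 | 0.516 | 83.2% | 90.4% | 32 |
| 0.8 | 0.632 | 94.7% | 97.5% | 22 |

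**Step 4: find the correlation that makes the sentence true.** At n = 34, 80% power needs dz = 0.495 two-sided or 0.435 one-sided. Solving for r:

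- Two-sided: r = 1 − (0.4 / 0.495)² / 2 = 0.67.
- One-sided: r = 1 − (0.4 / 0.435)² / 2 = 0.58.

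**Step 5: try a different test.** Consider a repeated-measures F test over the three time points with f = 0.2 (half of 0.4). The noncentrality is f² × n × 3 / (1 − r). At r = 0.6 this is 0.04 × 34 × 3 / 0.4 = 10.2, on 2 and 66 df, and power is 80.5%; the smallest n that reaches 80% is 34. At r = 0.5 power is 70.6%. At the same r = 0.6, the two-sided paired t test has 71.6% (Step 3).

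**The case against.** The strongest reply is that the sentence may be true. On the article's own definition of d, two-sided power passes 80% once r reaches about 0.67. The hypotheses are directional, and a one-sided test needs only r = 0.58. The three-time-point F test with r = 0.6 requires exactly 34, the design has three time points, and the abstract names a longitudinal model. A condensed article may also leave such inputs to a fuller document.

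Much of this stands. A reader might infer that the 80% is simply an error and that the true power is 62%. The article does not support that: 62% is the value at r = 0.5, or with d on the SD of the differences, and the article commits to neither.

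The reply does not rescue the sentence as written. Each route needs an input that the article does not state, and the F test is not planned in the analysis section. Nor is this only an omission, because the article makes an unconditional numerical claim that its stated test does not deliver without a favourable assumption.

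Two further inferences are tempting and also go too far. One is that a non-significant result would send the programme back to redesign. The Discussion ties that step to survivors not finding the study helpful, and sets no significance threshold for progression. The other is that power is the wrong basis for n. The article also relies on the audit of pilot sample sizes, and its primary outcomes are feasibility and satisfaction, so preferring a precision argument is a matter of choice.

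**Conclusion.** The stated 80% does not follow from the stated inputs for the planned paired t test. With d scaled by the SD of the differences, or with r = 0.5, power at n = 34 is about 62% two-sided and 74% one-sided. With d on the pooled SD and r between 0.3 and 0.7, two-sided power runs from 48% to 83%, and 80% is reached only at r of about 0.67 or more.

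These figures assume 34 complete pairs, alpha .05 and, for the pooled-SD results, equal SDs before and after. The correlations are assumptions, since the article gives none. The finding is that the claim is conditional and the condition is missing; it does not establish that the authors' calculation was wrong. It concerns the preliminary efficacy outcomes and leaves the feasibility objective untouched.

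**What to change.** Keep n and rewrite the power sentence:

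1. State that it refers to the planned test, and give the form of d, the sidedness and the assumed pre-post correlation with its justification.
2. If a correlation of at least about 0.67 (two-sided) cannot be justified, state that 34 complete pairs give 80% power at two-sided alpha .05 for a mean change of about 0.50 SD of the differences, and about 62% for 0.4.
3. Reconcile the paired t tests in the analysis section with the linear mixed models in the abstract, and make the power statement match whichever is kept.

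Optionally, add the precision of the feasibility rates. As an illustration, 31 of 38 retained (82%) has an exact 95% confidence interval of 66% to 92%.

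The cost is the rewording of one paragraph and of one line on the analysis method. No participants are added. Unless a high correlation can be supported, the stated power becomes less favourable.

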#### Eligibility Criteria

Inclusion criteria for participation are (1) history of any cancer diagnosis; (2) current age 10-17 years; (3) >2 years posttreatment or completed treatment and >5 years post diagnosis; (4) pain present over prior 3 months that impairs at least one area of daily life and occurs >1 per month; and (5) computer access, internet, and literacy. Survivors wishing to participate without a parent will not be excluded but will still require parental consent.

#### Patient Engagement

Patient engagement is an important component of health research. One systematic review found that across studies, engaging patients as partners in research increases enrollment and retention rates, and improves dissemination of results to be more meaningful and digestible for patient audiences [29]. The Canadian Institutes of Health Research Strategy for Patient Oriented Research Patient Engagement Framework [30] is a roadmap on how to engage patients as partners in health research, with the goal of improving health outcomes and creating a more enhanced health care system. The framework provides guiding principles (inclusiveness, support, mutual respect, and cobuilding of ideas), tools, and resources for researchers to use throughout their projects. It highlights that patients should be included from the start of the research project and that they should collaborate with the researchers as equal members of the team.

In this study, 3 patient partners were involved in the study design and will be involved in recruitment, interpretation of results, and knowledge translation for this study. More specifically, the patient partners have been consulted on the study protocol where they provided feedback and have approved the final version to be submitted to the institutional ethics committee. We started a group on Slack (Slack Technologies, Salesforce Inc), a web-based communication platform that allows us to share communications and materials all in 1 place. Patient partners will help with the creation and dissemination of recruitment materials, using their own connections with advocacy groups and Canadian cancer advocacy groups. Similar to previous experiences, we will discuss findings with patient partners in order to seek their interpretation of the results and how to communicate them. This work will foster inclusiveness, support, mutual respect, and cobuilding of ideas [30].

### Procedures

#### Recruitment

Survivors will be recruited from the Long-Term Survivors Clinic at the Alberta Children’s Hospital in Calgary, Alberta, Canada. The participant flowchart is in Figure 1. The study team will contact potentially eligible survivors by phone or email. Approximately 700 survivors receive follow-up care at ACH, and an estimated 240 of these survivors may be experiencing chronic pain based on our research [3]. Approximately 94% of Canadians have internet access at home [31] and recruitment rates from our previous pain-related research were 70% [3]. Conservatively, we expect 40% of these survivors to meet our inclusion and exclusion criteria, leaving a possible sample of 70. Meeting our targets would require a participation rate of 49% (34/70).

**Figure 1 figure1:**
[figure not shown]
Participant recruitment flowchart.

#### Data Collection

Upon enrollment and completion of informed consent, survivors and their parents will complete pretreatment questionnaires (T0) and be given access to WebMAP. Upon treatment completion (T1), survivors and parents will complete the same questionnaire battery plus the Treatment Evaluation Inventory—Short Form [32]. In addition, we will conduct posttreatment interviews to gather feedback on the program. Patient and caregiver partners will be involved in creating the interview questions and conducting a portion of the interviews. Interviews will be recorded and transcribed. Finally, survivors will be administered the same questionnaire battery at 3 months post intervention (T2) to assess longer-term effects of the intervention. Questionnaires will be completed over internet via Research Electronic Data Capture (REDCap) tools hosted by the University of Calgary Clinical Research Unit. REDCap is a secure, web-based application designed to support data capture for research studies, providing (1) an intuitive interface for validated data entry, (2) audit trails for tracking data manipulation and export procedures, (3) automated export procedures for seamless data downloads to common statistical packages, and (4) procedures for importing data from external sources. The investigator leading the trial (MP) and the sponsor (FS) will have access to the final trial data set (Table 1).

**Table 1 table1:** World Health Organization trial registration data set.

Data category			Information
Primary registry and trial identifying number			ClinicalTrials.gov NCT05241717
Date of registration in primary registry			February 4, 2022
Sources of monetary or material support			Alberta Children’s Hospital Trainee Small Research Grant^a^
Primary sponsor			[name]^a^, [contact]
Contact for public queries			[name], [contact]
Public title			Internet-delivered cognitive behavioral treatment for adolescent survivors of childhood cancer with chronic pain
Scientific title			Internet-delivered cognitive behavioral treatment for adolescent survivors of childhood cancer with chronic pain: A pilot feasibility trial
Countries of recruitment			Canada
Health conditions or problems studied			Cancer, chronic pain

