##### Feasibility

Feasibility will be assessed by considering rates of: (1) recruitment, (2) retention, (3) treatment engagement, (4) acceptability, and satisfaction. “Recruitment” will be measured by the number of survivors enrolled or consented divided by the total number of survivors invited to participate. Based on previous trials of similar nature [17], a 50% recruitment rate of eligible survivors will be used as the benchmark to determine this factor of study feasibility. “Retention” will be measured by the number of survivors who complete the study defined as those who complete the intervention and all assessments from enrollment (T0) to 3-month follow-up (T2) divided by the total number of survivors who enrolled in the study. Survivors will be considered to be enrolled in the study when they have read and signed the informed consent form. Based on previous pilot trials [17], an 80% retention rate will be considered “feasible.” “Treatment engagement” will be measured by number of modules completed by survivors and parents. Based on similar trials [17], the goal to determine treatment engagement will be at least 75% of survivors completed at least 6 of the 8 modules, and the mean number of modules completed by the sample being at least 6. We hypothesize that >75% of survivors will complete assessment measures across the 3 specified time points. “Acceptability” will be measured using the Treatment Evaluation Inventory—Short Form (TEI-SF) [32], a 9-item self-report measure of acceptability of treatment, completed by both survivors and parents. The TEI-SF was originally designed to measure parents’ acceptability of a treatment for children with problem behaviors but has been adapted to assess the acceptability of WebMAP in previous studies [17]. Responses are scored on a 5-point Likert scale and summed to create a total score. Higher scores represent better acceptability. Moderate to high acceptability, defined as a score of 27 or higher, has been considered sufficient for trials of similar nature [17,33]. The TEI-SF has good reliability and validity across various child treatments [32]. This study will use the adapted version and will be completed by survivors and parents.

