##### Satisfaction

A survey including open-ended questions will be created with patients to elicit feedback on specific modules. These questions will ask about what information was helpful and what may need to be adjusted to better serve youths with a history of cancer for both patients and parents. The satisfaction survey will be completed as part of the posttreatment questionnaire by survivors and parents.

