##### Qualitative Interviews

Semistructured interviews will be conducted with survivors and parents separately upon treatment completion to assess feasibility, acceptability, and satisfaction with the program. Patient partners will be involved in creating an interview guide. The interview guide will include open-ended questions about participants’ experience with the program to facilitate self-reflection and open discussion around important aspects of their experience. Interviews will be audio-recorded and transcribed verbatim.

#### Objective 2

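### T1 and all acceptability measures are worded as following treatment completion, with no stated route for early stoppers, so acceptability may rest mainly on completers

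*Protocol article*

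**What the plan says.** Acceptability is part of the primary objective (end of the Introduction) and a component of feasibility (Feasibility section). Table 1 lists feasibility and satisfaction as the primary outcomes. Three sources inform acceptability and satisfaction: the TEI-SF, a satisfaction survey and interviews.

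Most of the timing statements point to completion:
- Data Collection: "Upon treatment completion (T1), survivors and parents will complete the same questionnaire battery", with the TEI-SF added to the battery.
- Qualitative Interviews: "Semistructured interviews will be conducted with survivors and parents separately upon treatment completion". Study Design agrees: "Individual interviews will also be conducted upon completion of the intervention".
- Satisfaction: "The satisfaction survey will be completed as part of the posttreatment questionnaire by survivors and parents".
- Study Design counts T2 as three months from completion of the intervention.

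Two statements can be read as a calendar point instead. Study Design places T1 "immediately following the intervention (T1"), and the Abstract says "After the 8-week intervention, survivors will complete the same measures (T1").

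The Feasibility section describes the TEI-SF as "a 9-item self-report measure of acceptability of treatment, completed by both survivors and parents", with 5-point items that are summed. It treats "Moderate to high acceptability, defined as a score of 27 or higher" as sufficient. It gives neither the item codes nor whether 27 applies to a mean or to a share of respondents. Separate benchmarks cover retention (80% of enrolled survivors complete the intervention and every assessment) and engagement (75% of survivors complete at least 6 of 8 modules).

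**The concern.** Every acceptability source sits behind the same event. If that event is finishing the programme, someone who leaves halfway is never prompted to say why. Completion is also not defined. The engagement goal is met at 6 of 8 modules, so even a survivor who satisfies it might not count as having completed treatment.

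The people missed are likely to include those who found the programme least acceptable. The Discussion itself expects that milder pain may weaken motivation to engage. It also makes the next step depend on these data: return to the design phase for tailoring if survivors do not find the programme helpful, or move to an efficacy trial if it is feasible, acceptable and promising. Early leavers are well placed to say what needs tailoring. A second consequence is that T1 and T2 would fall at different calendar times for fast and slow users.

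**Working it through.** **1. Which trigger applies?** Set side by side, Data Collection and Qualitative Interviews name completion of treatment, Study Design names completion for the interviews and for T2, and Study Design (for T1) and the Abstract allow a time-based reading. No section says that a person who stops early receives the TEI-SF, the survey or an interview invitation.

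**2. How many survivors could be unheard?** Inputs are the recruitment target of 38 and 10% attrition (Sample Size) and the 80% retention benchmark (Feasibility).
- Check of the plan's figure: 34 / 0.90 = 37.8, rounded up to 38. It reproduces.
- Retention just met: 0.80 × 38 = 30.4, so at least 31 are retained and at most 7 are not (7/38 = 18%). A retained survivor has by definition completed every assessment, so 7 is the ceiling on missing survivor scores when the benchmark is met.
- Loss of no more than 10%: 0.90 × 38 = 34.2, so at least 35 respond and at most 3 are missing.

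**3. Effect on the mean.** The plan gives no calculation behind 27, so there is none to reproduce. Assumptions: 27 is applied to a mean, items are coded 1 to 5 (range 9 to 45), the respondent mean is exactly 27, and each missing person would have scored *s*. Two values of *s* are shown: 9 (the minimum) and 18 (an average of 2 per item).

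All-enrolled mean = (27 × responders + *s* × missing) / 38. Respondent mean needed for an all-enrolled mean of 27 = (27 × 38 − *s* × missing) / responders.

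| Responders / missing | *s* | All-enrolled mean | Respondent mean needed |
|---|---|---|---|
| 31 / 7 | 9 | (837 + 63)/38 = 23.7 | (1026 − 63)/31 = 31.1 |
| 31 / 7 | 18 | (837 + 126)/38 = 25.3 | (1026 − 126)/31 = 29.0 |
| 35 / 3 | 9 | (945 + 27)/38 = 25.6 | (1026 − 27)/35 = 28.5 |
| 35 / 3 | 18 | (945 + 54)/38 = 26.3 | (1026 − 54)/35 = 27.8 |

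Taking the plan's 34 evaluable of 38 instead gives (918 + 36)/38 = 25.1 or (918 + 72)/38 = 26.1.

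**4. Sensitivity to item coding.** Coded 1 to 5, the midpoint is 9 × 3 = 27. Coded 0 to 4, the range is 0 to 36, the midpoint is 9 × 2 = 18, and 27 is 27/36 = 75% of the range. The minimum is then 0, and the worst case becomes 837/38 = 22.0 with 31 responders or 945/38 = 24.9 with 35. So the non-response point holds under either coding; the midpoint point does not.

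**The case against.** The strongest reply is that T1 may already be a calendar time point. The Abstract and Study Design allow it, and the Feasibility section treats finishing modules and finishing assessments as different things: retention requires both, and assessment completion has its own hypothesis. A condensed article may also leave assessment windows and contact after early stopping to the full protocol. This stands to the extent that a reader who infers that early stoppers are definitely excluded goes too far. It does not remove the inconsistency, because the section that governs data collection names treatment completion.

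A second reply is that dropout is visible in the retention rate, which uses all enrolled survivors as its denominator. That is correct and limits the size. But the rate counts leavers without recording their opinions, covers survivors and not parents, and bounds the loss only if every benchmark must be met together, which the article does not say.

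Three stronger inferences are not supported:
- A reader might multiply an assumed satisfaction rate by the 75% engagement goal to get a share of satisfied enrollees. That treats survivors with fewer than 6 modules, non-respondents and dissatisfied users as the same people, and no proportion-based acceptability criterion is stated.
- A reader might say that 27 is the neutral score and that indifferent users pass. That needs coding of 1 to 5, which is not stated; other 5-point scales in the article use 1 to 5 (PROMIS) and 0 to 4 (insomnia, parental responses).
- A reader might conclude that pre-post changes are also biased upward. The article does not show this; someone who stops because the pain has resolved would push the other way.

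**Conclusion.** The point holds as a contradiction in the definition of T1 with a consequence for a primary outcome. Followed literally, the completion wording measures acceptability mainly in completers, and the result is probably too favourable. The direction rests on the assumption that early leavers are less satisfied; the article gives no data on this.

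Under the stated assumptions (threshold applied to a mean, coding 1 to 5), a respondent mean at the threshold overstates the all-enrolled mean by 0.7 points (27 − 26.3) to 3.3 points (27 − 23.7), depending on how many are missing and how they would score. These are illustrative bounds, not estimates. A respondent mean above 31.1 would keep the all-enrolled mean above 27 even in the worst of the tabulated cases.

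The midpoint issue is secondary and conditional. If items are coded 1 to 5, all-neutral answers sum to 27 and meet the threshold; if 0 to 4, it does not apply. Either way it gives no good reason to move the cut-off. A rule of above 27 changes little and loses comparability with the trials from which the article takes its threshold.

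**What to change.** - Define T1 the same way throughout: a fixed time, 8 weeks after access to the programme with a stated window, for every enrolled survivor and parent whatever the number of modules completed. Define T2 as three months after that date.
- Invite non-completers to the TEI-SF, the satisfaction survey and the interview.
- Report acceptability with the number of enrolled who responded, separately for completers and non-completers, and add a sensitivity analysis on the enrolled denominator. Do this for survivors and parents separately.
- State the item coding and whether 27 applies to a mean or to a proportion. If coding is 1 to 5, show the score distribution beside the threshold.

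The cost is small: a wording amendment through the ethics board, date-based invitations in the REDCap system already in use, and some extra interviews. Enrolment is already under way, so participants assessed under the existing wording should be identified in the report. The main downside is that some T1 ratings will come from people still mid-programme; recording modules completed at T1 lets these be shown separately.
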